## Abstract

**Introduction:**

Antibiotic consumption is highest in primary care, and antibiotic overuse furthers antimicrobial resistance. In our recently published pilot-RCT, we used monthly aggregated claims data to provide personalized antibiotic prescription feedback to general practitioners (GPs). The pilot-RCT has shown that personalized prescription feedback is a feasible and promising low-cost intervention to reduce antibiotic prescribing. Here, we describe the rationale and design of the follow-up RCT with 3426 GPs in Switzerland. We now have access to pseudonymized patient-level data from routinely collected health insurance data of the three largest health insurers in Switzerland.

**Methods and analysis:**

1713 GPs randomized to the intervention group received once evidence-based treatment guidelines at the beginning, including region-specific antibiotic resistance information from the community and personalized feedback of their antibiotic prescribing, followed by quarterly personalized prescription feedback for two years. The first and the last mailings were sent out in December 2017 and September 2019, respectively. The 1713 GPs randomized to the control group were not notified about the study and they received no guidelines and no prescription feedback. The personalized prescription feedbacks and the analyses of the primary and secondary outcomes are entirely based on pseudonymized patient-level data from routinely collected health insurance data. The primary outcome is prescribed antibiotics per 100 patient consultations during the second year of intervention. The secondary outcomes include antibiotic use during the entire two-year trial period, use of broad-spectrum antibiotics, hospitalization rates (all-cause and infection-related), and antibiotic use in different age groups. If the feedback intervention proves to be efficacious, the intervention could be continued systemwide.

**Ethics and dissemination:**

The trial is publicly funded by the Swiss National Science Foundation (SNSF, grant number 407240_167066). The trial was approved by the ethics committee "Ethikkommission Nordwest-und Zentralschweiz" (EKNZ Project-ID 2017-00888). Results will be disseminated in peer-reviewed journals and international conferences.

## Background

1

Antibiotic resistance is a serious problem worldwide [1] and directly related to antibiotic consumption [[2], [3], [4]]. In absolute terms, most antibiotics are prescribed in primary care for respiratory and urinary tract infections, which represent the most frequent reasons for physician contact and antibiotic prescribing [[5], [6], [7], [8]].

Strategies to lower antibiotic use in primary care on the system level are difficult to implement. Efficacious strategies to reduce antibiotic prescribing, like face-to-face education or communication training of primary care physicians, are resource-intense, costly, and challenging to apply on a large scale [9,10]. Systemwide feedback interventions on antibiotic prescribing are less resource-intense and low-cost interventions [[11], [12], [13]]. Only a few randomized controlled trials (RCTs) have evaluated feedback interventions for antibiotic prescribing in primary care. These trials have produced inconsistent results. Two trials from the UK, one intervening with a letter from the UK Chief Medical Officier to inform general practitioners (GPs) of practices with the highest 20% on their high prescribing rates [11], and the second trial, sending monthly feedback on antibiotic prescription to GPs for 12 months, both trials lead to moderate reductions in antibiotic prescribing [13].

A trial from Australia found no effect on antibiotic prescription rates from two feedbacks on antibiotics and other drug prescribing that were sent to unselected GPs [14]. In a nationwide trial in Switzerland [12] by our group, the provision of quarterly personalized prescription feedback to primary care physicians over two years did not result in a reduction of antibiotic use (in defined daily doses per 100 consultations) between the intervention and the control group (between-group difference: 0.8% in the first year; 95%CI -2.6%–4.3%; 1.7% in the second year; −5.1%–1.7%), but reduced prescriptions in predefined subgroups of older children and adolescents aged 6–18 years (−8.6% in the first year; 95%CI -14.8% to −1.9%) and younger adults (−4.6% in the second year; 95%CI -7.9% to −1.2%).

Switzerland belongs to the countries with the lowest antibiotic consumption rates in Europe [[15], [16], [17]]. However, prescriptions of antibiotics in primary care are still too high for upper respiratory tract infections, and the high use of quinolone for urinary tract infections is a matter of concern [18]. Also, the emergence of multidrug resistance remains a problem [19].

Here we present the study design of a pragmatic nationwide randomized controlled trial, which assesses a feedback intervention of antibiotic prescribing over two years using patient-level data from routinely collected health insurance claims data. The use of patient-level data will also allow for the monitoring of eventual negative health outcomes like reconsultations and hospitalization. Our intervention targets primary care physicians in Switzerland with average to high antibiotic prescription rates.

## Methods/design

2

### Study design and objective

2.1

This is a pragmatic randomized controlled trial in primary care physicians in Switzerland with average to high antibiotic prescription rates. The trial is entirely based on routinely collected individual claims data of the three largest Swiss health insurers (Sanitas, CSS, and Helsana) using pseudonymized identifiers of physicians and patients.

The primary objective is to investigate the effect of a quarterly prescription feedback intervention on the overall antibiotic use in primary care in the second year of intervention (long-term effect). Secondary objectives are to assess effects on the overall antibiotic use within the first 12 months and the entire 24 months intervention duration, and in different age groups. Further secondary objectives address the use of broad-spectrum antibiotics and the impact of the intervention on the eventual unintended effects on hospitalization (all-cause and infection-related) and reconsultation rates.

### Inclusion and exclusion criteria

2.2

We included and use data from board-certified primary care physicians (Foederatio Medicorum Helveticorum, FMH) in Switzerland with an individual practicing license number "Zentralregisternummer" (ZSR) who are the top 75% prescribers of antibiotic and who have at least 100 patient contacts per year. Group practices sharing a license number are excluded.

### Study population, sample size, and power analysis

2.3

The data provided by the three health insurers Sanitas, CSS, and Helsana, comprise information on a total of 8422 primary care physicians in Switzerland. These primary care physicians treated at least one patient covered by one of the three health insurances. Due to the usual administrative processing delay of claims data of 6 months by health insurers, the definitive sample size calculation had to be based on claims data from January to December 2016. In this pre-randomization claims data set, we identified 3646 eligible GPs corresponding to the inclusion criteria, as mentioned above. A random sample of 220 physicians from the Basel area was left aside for a different interventional trial. The remaining study population of 3426 physicians were randomized to the intervention or control groups, with 1713 physicians in each arm.

We conducted a power analysis that was based on a trial simulation from 50 bootstrap samples. These bootstrap samples were extracted from the pool of physicians from the database of the year 2016, which was used to select and randomize GPs. The clinically relevant effect that the study aims to detect is, on average 5% expected reduction in prescription rates. Therefore, we simulated a trial for each bootstrap sample and we applied the effect which we expected to observe in the treatment arm. To also account for any variability, we simulated effects from distribution of potential effects, which were "centered" around 5%, for every physician. The standard deviation of the prescription rate in the target population was evaluated based on the data from the year 2016, which was 0.059 on the raw scale and 0.438 on the log scale. Also, we scaled the distribution to account for the expected proportion of non-responders of 15%. For each sample, we then tested the difference using a Mann Whitney *U* test (Wilcoxon rank-sum). Hence, we evaluated the power for each bootstrap sample, and derived medians and confidence intervals from the empirical distribution, which gave an estimated median power of 0.93 (95% CI: 0.90 to 0.96).

### Randomization, treatment allocation, and blinding

2.4

All 3426 GPs were randomly allocated by a 1:1 ratio to the intervention and control group using R (R Core Team 2017 [20]). GPs in the intervention groups were formally blinded concerning the trial design, and GPs in the control group were fully blinded.

As all RCT relevant data are routinely collected by the automated procession of claims data of health insurances, the outcome assessment may also be considered as formally blinded.

Data analysis will be conducted by a statistician blinded for group assignment of physicians in the trial.

### Intervention and control

2.5

The first mailing was sent on December 22, 2017 and was followed by seven additional quarterly mailings, with the last mailing sent in late September 2019 (see the timeline in Fig. 1). With the first mailing, all GPs in the intervention group received (1) an accompanying letter explaining the intervention, assuring the full pseudonymization of feedback data, (2) a personalized feedback of antibiotic prescribing; (3) a response card for physicians wishing to opt-out; and (4) evidence-based guidelines on antibiotic prescribing for respiratory and urinary tract infections (see details below). No information on the study design or comparative study purpose was provided.

**Fig. 1 fig1:**
[figure not shown]
Time periods when claims data were used for general practitioners selection and randomization, for feedback preparation and intervention, and for baseline and outcome assessment.

In the second feedback mailing in April 2018, information on antibiotic resistance data and its regional distribution from the Swiss Centre for Antibiotic Resistance [19] was added.

### Personalized antibiotic prescribing feedback

2.6

The personalized antibiotic prescription feedback contained 1) the personal yearly prescription rate (antibiotic prescriptions per 100 consultations) compared with the prescription rates of the peer-physicians, 2) the personal monthly prescription rates for the three months for the same period of the preceding year and its comparison with peer-physicians (the first feedback mailing was based on antibiotic prescription rates between April 2016 to March 2017), 3) the personal yearly prescription rate (antibiotic prescriptions per 100 consultations) stratified by type of antibiotics and compared with the prescription rates of peer-physicians, and 4) a call to action information in a blue box, which varied with each mailing (see example Fig. 2). Personalized antibiotic prescription feedback was provided every three months in the form of a postal mailing and was continuously updated with the most recent complete health insurance data. As there is a six months delay in the health insurance billing records processing and the time needed to prepare the feedbacks, the yearly prescription feedbacks were based on the data from the period of 9 month prior to each sent mailing. All information material and guidelines were also made available to physicians on a password-protected trial website.

**Fig. 2 fig2:**
[figure not shown]
Example of a antibiotic prescribing feedback form.

### Evidence-based guidelines

2.7

Evidence-based guidelines for the management of upper and lower respiratory tract and urinary tract infections were provided once with the first mailing to the GPs in the intervention arm. We updated our guidelines from our previous pilot-RCT [12,21] with systematic literature research for additional evidence on the effectiveness of antibiotics for the treatment of these conditions for the time period of 2013 until June 2017. Also, we evaluated the literature on the effectiveness of relevant diagnostic tests for the identification of bacterial-related upper and lower respiratory tract infections in primary care. The guidelines for upper respiratory tract infections were updated together with an expert group by the Swiss Society of Infectious Diseases that is responsible for the development of Swiss national guidelines for the treatment of upper respiratory and urinary tract infections. The guidelines were provided as a paper brochure with the first mailing at the end of December 2017 to all physicians in the intervention group.

Because more than 90% of physicians' offices are located in the German- and French-speaking regions of Switzerland, we provided all information in these two official languages. We assumed that most physicians in the Swiss Italian part know either French or German, since the Swiss educational system includes German or French, and as there is not yet a medical school in the Swiss Italian part of Switzerland.

### Outcomes

2.8

The primary outcome is the overall antibiotic use, defined as prescribed antibiotics per 100 patient consultations in the second year of intervention lasting from month 13 to month 24 (long-term intervention effect).

The secondary outcomes are (1) overall antibiotic use defined as prescribed antibiotics per 100 patient consultations from month 1–12 (first year of intervention, shorter-term intervention effect); (2) overall antibiotic use defined as prescribed antibiotics per 100 patient consultations over the entire intervention period from month 1 to month 24, with two repeated measurements, over the first and the second 12 month period of intervention; (3) use of broad-spectrum antibiotics (quinolones and oral cephalosporines) per 100 patient consultations; (4) hospitalizations rates (all-cause and related to infections based on Diagnosis Related Groups (DRG) definition); (5) Antibiotic use (prescribed antibiotics per 100 patient consultations) in five specific age groups, in patients 0–14 years, 15–24 years, 25–54 years, 55–64 years, and ≥65 years; and (6) secondary outcomes (3) to (5) will be evaluated separately over the second and first 12 months (from month 13 to month 24 and 1–12 months).

All cause hospitalization will be defined as any hospitalization (DRG-based) within 30 days after a preceeding GP consulation. Infection-related hospitalization will be defined as any hospitalization within 30 days after a preceeding GP consulation with DRG-codes for community acquired pneumonia, urinary sepsis, or sepsis. Reconsultation will be defined as any consultation within 30 days after a first GP consultation or any emergency consultation in a hospital.

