Antibiotics	Date of the prescription, all pharma codes from ATC group J01, complete ATC code (ATC group J01), number of prescribed packages, total costs according to claims in CHF, costs per packages in CHF
Table 1e) Inpatient information	
Hospitalization	Date of hospital admission, date of hospital discharge, DRG code(s)

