### Data analysis

2.11

Statistical analysis will be performed by the trial statistician using R (R Core Team 2017 [20]). All analyses will be conducted using the final dataset, which will be available in September 2020 (see also timeline in Fig. 1C) and will follow CONSORT guidelines and intention-to-treat principles [[22], [23], [24]]. A flowchart will describe the inclusion and follow-up of GPs by study arm. Baseline characteristics will be described by study arm with summary statistics such as median and interquartile range or number and percentage; no formal testing between arms will be performed [25]. Outcomes will be described by arm using summary statistics.

The primary outcome, the proportion of individuals with an antibiotic prescription in the second year of the intervention, will be assessed by ANCOVA modeling, with the outcome as a response, intervention (yes/no) as a factor of interest, and baseline year antibiotic prescription rate as a covariate (the baseline year is January–December 2017). Other baseline covariates of interest include comorbidities (based on pharmacy cost groups) patients' age, annual patient volume (total number of consultations per GP), and seasonality. For the primary outcome analysis, the coefficient estimates and their 95% CI will be reported. Secondary outcomes will be evaluated in the same way.

Effects for the period month 1 to month 24 will be modeled using a linear mixed model including the intervention (yes/no), time (baseline, first year, second year), an interaction term for the intervention with time, and by treating physician as random effects. Mean percentage changes from baseline will be derived for the intervention and control groups. Other baseline covariates of interest will be included as for the primary analysis.

The rates of hospitalizations and reconsultations will be modeled using logistic regressions including the intervention as a factor of interest and other relevant covariates. Hospitalization rates in the intervention and control group, with exact 95% CIs will be reported, and odds ratios for the intervention arm vs. control will be derived from the coefficients estimated for the logistic regression model.

The analysis in specific age groups will be similar to the primary analysis over the respective periods and stratified by age groups i) 0–14 years, ii) 15–24 years, iii) 25–54 years, iv) 55–64 years, and v) 65 years and over.

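### Both hospitalization harm outcomes count an admission only if a GP visit preceded it by at most 30 days, so an intervention effect on visiting could shift the harm comparison with no change in true admissions

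*Protocol article*

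**What the plan says.** Section 2.8 (Outcomes) defines the two hospitalization outcomes through a preceding visit: "All cause hospitalization will be defined as any hospitalization (DRG-based) within 30 days after a preceeding GP consulation", and "Infection-related hospitalization will be defined as any hospitalization within 30 days after a preceeding GP consulation with DRG-codes" for a short list of severe infections. Both are assessed by trial year: "secondary outcomes (3) to (5) will be evaluated separately over the second and first 12 months". The visits that open the 30-day windows therefore fall after randomisation, except possibly a few just before month 1.

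Section 2.1 (Study design and objective) gives these outcomes their role. They are there to show "the impact of the intervention on the eventual unintended effects on hospitalization (all-cause and infection-related) and reconsultation rates". Visiting is thus itself a possible intervention effect, with its own definition in 2.8: "Reconsultation will be defined as any consultation within 30 days after a first GP consultation or any emergency consultation in a hospital".

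Section 2.11 (Data analysis) says: "The rates of hospitalizations and reconsultations will be modeled using logistic regressions". It does not say whether a patient, a consultation or a GP is the unit. Consultation volume per GP appears in that section only among the baseline covariates. Table 1e in section 2.10 lists admission dates, discharge dates and DRG codes. No hospitalization measure free of the visit trigger is defined anywhere in the article.

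**The concern.** The definition selects events by something the intervention may change. On a per-patient count, more return visits open more windows and catch more admissions that would have happened anyway. Fewer visits close windows and hide admissions. On a per-consultation rate, a change in the mix of visits alters the denominator. In each case the odds ratio can move with no change in true admissions. A baseline volume covariate cannot absorb a change that arises after randomisation.

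Separately, a patient who goes straight to hospital more than 30 days after the last visit is invisible in both arms. For an outcome meant to pick up harm from withheld antibiotics, that is a gap in coverage. At stake is whether a null or positive harm result can be read as a statement about admissions.

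**Working it through.** The article gives no figure for hospitalization or for visits per patient, so there is no plan figure to reproduce. The visit rates below are assumptions, shown as a range.

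**1. Per-patient count.** Let visits occur at random at rate c per patient-year, independent of admissions. The share of admissions with a visit in the preceding 30 days is f(c) = 1 − exp(−c × 30/365).

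Example: f(4) = 1 − exp(−0.329) = 0.280 and f(4.2) = 1 − exp(−0.345) = 0.292. The ratio is 1.042, so 5% more visits raise counted admissions by 4.2%.

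| Assumed visits per year | Share of admissions counted | 5% more visits | 10% more visits | 10% fewer visits |
|---|---|---|---|---|
| 2 | 15% | +4.6% | +9.1% | −9.3% |
| 4 | 28% | +4.2% | +8.3% | −8.6% |
| 8 | 48% | +3.5% | +6.8% | −7.3% |

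A simulation of 3 million patients with a true rate of 0.10 admissions per patient-year agrees. At 3.6, 4.0 and 4.4 visits per year the counted rate was 0.0247, 0.0268 and 0.0292. The true rate stayed at 0.100. The simulated levels lie slightly below 0.10 × f(c) because visits before the start of the year were not generated.

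**2. Per-consultation rate.**
- *Every consultation assessed for an admission in its own window, windows may overlap, equal risk at each visit:* no shift. The simulated proportions were 0.0079, 0.0078 and 0.0079 at 3.6, 4.0 and 4.4 visits.
- *Each admission counted once and divided by consultations:* 5% more visits lower the rate by 0.4% (2 visits a year) to 1.4% (8 visits). At 4 visits this is 1.042/1.05 = 0.992.
- *Visit mix changes:* if 10% of consultations disappear and these carried half the usual risk, the rate rises by 1/(0.90 + 0.10 × 0.5) − 1 = 5.3%. If they carried none, it rises by 1/0.90 − 1 = 11.1%.

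Fewer visits therefore lower the per-patient count but leave unchanged or raise the per-consultation rate.

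**3. A scale from the article's own figures.** Section 2.3 gives the SD of the prescription rate as 0.059 (raw) and 0.438 (log), and a targeted average reduction of 5%. If the rate is log-normal, its mean is 0.059/√(exp(0.438²) − 1) = 0.059/0.460 = 0.128 per consultation. A 5% reduction is 0.05 × 0.128 = 0.0064, or about 0.64 avoided prescriptions per 100 consultations. If every avoided prescription produced one extra visit, visits would rise by about 0.64%.

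For small changes, the relative shift in f(c) is the relative change in visits times x·exp(−x)/(1 − exp(−x)), with x = c × 30/365. That factor is 0.92 at c = 2 and 0.71 at c = 8. The shift is 0.64% × 0.92 = 0.59% and 0.64% × 0.71 = 0.45%, or roughly 0.5-0.6%.

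**The case against.** The strongest reply is that the window has a purpose. Section 3 (Discussion) is concerned with consequences of untreated bacterial infection, and a 30-day window ties an admission to a GP's decision. Counting every admission dilutes that signal. This stands, and it is why the definition should be kept.

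Second, the outcome is indexed to a consultation and modelled by logistic regression, so a consultation-level analysis is a natural reading. With equal risk at each visit, that analysis does not move. This also stands, but it needs equal risk. The assumption is doubtful if the visits that change are mainly minor infections, and admissions without a recent visit stay uncounted either way.

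Third, reconsultation is analysed alongside, so a change in return visits would be partly visible. It would show that visiting had shifted, but not what admissions did.

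A reader might go further in four ways that the article does not support:
- *The harm comparison is biased.* Nothing in the article shows that visit rates differ by arm, and fewer visits through patients learning not to consult is not mentioned.
- *The shift rivals the 5% effect the trial is built to detect.* That 5% is the target for antibiotic prescribing, a different outcome. No margin for hospitalization is stated.
- *One admission may be counted in both arms.* That depends on an attribution rule the article does not give. Such a rule, like the unit of analysis, may properly sit in an analysis plan that is not shown.
- *The 30-day measure should be replaced.* Table 1b lists no insurance start or end dates and no death date, so a patient-year rate may not be available as a straight substitute. Choosing between the two measures is a choice between imperfect estimands.

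**Conclusion.** The point holds as a risk of bias that follows from a stated definition. Both hospitalization outcomes are conditioned on behaviour after randomisation that the protocol treats as a possible intervention effect, and no unconditioned measure stands beside them.

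The size is uncertain and may be small. The 3.5-4.6% shift rests on a per-patient unit, random visits independent of admissions, and an assumed 5% change in visits that nothing in the article supports. The one-extra-visit scenario, tied to the article's own figures, gives about 0.5-0.6%. It covers only that route, assumes log-normality, and is not an upper bound on other changes in visiting. The special consultation-level case gives none.

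The counted shares of 15% to 48% are probably too low, because in practice visits cluster before admissions. The exclusion of admissions without a recent visit does not depend on any of these assumptions.

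**What to change.** Keep the 30-day definition. In 2.8 and 2.11, add a co-reported harm analysis of all-cause and infection-related admissions regardless of any preceding visit:

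- Fix the patients from the 2017 baseline claims.
- Assign each patient to the GP with most of that patient's 2017 consultations, and analyse by that GP's arm.
- Use any admission per patient per period as the outcome, or admissions per patient-year if coverage dates can be obtained.
- Report consultations per patient by arm beside both measures, so the reader can see whether the trigger could have mattered.

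In the simulation, counting admissions this way left the rate at 0.100 whatever the visit frequency.

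The cost is extra programming and a check with the insurers that the Table 1e extract includes admissions with no prior visit. New patients, including children born after 2017, are excluded from this analysis, and admissions unrelated to GP care add noise. These drawbacks are acceptable for a measure reported beside the 30-day one.
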